#### Statistical analysis

All baseline continuous variables between groups will be compared using general linear modelling, whilst categorical variables will be compared using exact logistic regression. The rates of change will be estimated for each patient separately by linear regression. general linear modeling, will be used to compare the mean rate of change in primary outcome measures between groups, unadjusted and adjusted for actual and potential confounding variables. Mean differences, 95% confidence intervals and P-values will be corrected for repeated measures, and P-values corrected for multiple comparisons by the Holm method. All analyses will be performed using Stata/IC 10.1 for Windows (StataCorp LP, College Station, Tx).

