**Methods:**

This is an observational study. Eighty stage five CKD patients will be enrolled and followed for one-year. Primary outcome measures will be changes in 1) arterial stiffness measured by aortic pulse wave velocity, 2) oxidative stress assessed by plasma F_2 _isoprostanes and 3) inflammation measured by plasma pentraxin-3. Secondary outcomes will include additional measures of oxidative stress and inflammation, changes in vascular function assessed using the brachial artery reactivity technique, carotid artery intimal medial thickness, augmentation index and trans thoracic echocardiography to assess left ventricular geometry, and systolic and diastolic function. Patients will undergo these measures at baseline (6–8 weeks prior to starting dialysis therapy), then at six and 12 months after starting dialysis.

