#### Sample Size Estimates

Data from other studies indicates that pentraxin-3 has the highest variability of the three primary outcome measures (mean ± SD; isoprostanes = 54.1 ± 7.0 [46], PWV = 11.4 ± 2.4 [47], pentraxin 3 = 0.75 ± 0.3 [48]) and therefore will be used to estimate the sample size required. We assume that a decrease of 10% in pentraxin-3 would be clinically significant. Therefore, with alpha = 0.05 and beta = (1–0.8), we would need 23 patients in one of the groups. It is expected with an initial enrolment of 80 patients, 60 will complete the one-year measures. Based on the current distribution patterns within the renal services we estimate that 37 of these patients will be receiving haemodialysis and 23 receiving peritoneal dialysis.

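### The sample size assumes one test at alpha 0.05 and makes no allowance for the Holm correction that the analysis applies, so 80% power is not delivered under the plan's own testing rule

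*Protocol article*

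**What the plan says.** The Abstract lists three co-equal primary outcomes: "Primary outcome measures will be changes in 1) arterial stiffness measured by aortic pulse wave velocity, 2) oxidative stress" (measured by plasma F2-isoprostanes), and inflammation measured by plasma pentraxin-3. Table 1 repeats the three.

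Sample Size Estimates picks pentraxin-3 as the most variable of them ("pentraxin 3 = 0.75 ± 0.3"). It sets the target as follows: "We assume that a decrease of 10% in pentraxin-3 would be clinically significant". It then calculates "with alpha = 0.05 and beta = (1–0.8"), that is, 80% power, and concludes that "we would need 23 patients in one of the groups". From 80 enrolled it expects 60 completers, 37 on haemodialysis and 23 on peritoneal dialysis. Multiplicity is not mentioned there.

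Statistical analysis estimates a rate of change for each patient, compares the mean rates between groups for the primary outcomes, and has "P-values corrected for multiple comparisons by the Holm method". It does not say which comparisons form the Holm family.

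**The concern.** The article fixes both the alpha used for sizing and the rule used for testing, and the two do not match. With three primary comparisons under Holm, the smallest P-value must reach 0.0167, the next 0.025, and only the last is tested at 0.05. The stated 80% therefore belongs to a single uncorrected test that the plan will not run.

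What is at stake is how a null result is read. The Abstract says that the findings may guide choice of dialysis modality and may lead to a larger study. If a Holm-adjusted null result is set against a claimed 80% power, it will look more informative than it is.

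**Working it through.** **Inputs.** From Sample Size Estimates: pentraxin-3 0.75 ± 0.3, isoprostanes 54.1 ± 7.0, PWV 11.4 ± 2.4, a 10% difference, alpha 0.05, power 80%, 37 v 23 completers. Assumptions: two-sided tests (sidedness is not stated), a Holm family of the three primary outcomes, and the quoted SDs of levels standing in for the SD of the rate of change, which is not given.

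**1. The plan's own figure.** The standardised difference is d = 0.075/0.3 = 0.25. At a ratio of 37:23, the smaller group needs

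n = (1 + 23/37) × (1.960 + 0.842)² / 0.25² = 1.622 × 7.849 / 0.0625 = 203.6, so 204.

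At 1:1 it is 2 × 7.849 / 0.0625 = 251.2, so 252 per group. One-sided tests give 161 and 198. A one-sample calculation gives 126 (two-sided) or 99 (one-sided). None of these gives 23. The isoprostane inputs come close: d = 5.41/7.0 = 0.773 gives 1.622 × 7.849 / 0.597 = 21.3, so 22.

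Power for pentraxin-3 at 37 v 23: √(1/37 + 1/23) = 0.2655 and 0.25/0.2655 = 0.942.
- At 0.05: Φ(0.942 − 1.960) = 15%.
- At 0.0167: Φ(0.942 − 2.394) = 7%.

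**2. Effect of the Holm threshold, with 80% at 0.05 granted.** With 37 v 23 (58 df), d = 0.757 gives exactly 80% at two-sided 0.05; the noncentrality is 0.7565/0.2655 = 2.849.

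| Holm step | Threshold | Critical t | Power at d = 0.757 |
|---|---|---|---|
| First | 0.0167 | 2.465 | 65.0% |
| Second | 0.025 | 2.301 | 70.7% |
| Third | 0.05 | 2.002 | 80.0% |

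Normal check for the first step: Φ(2.802 − 2.394) = 65.8%. Restoring 80% there would multiply the sample by (2.394 + 0.842)²/(1.960 + 0.842)² = 1.334. In the smaller group that is 23 × 1.334 = 30.7, so 31.

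**3. The full Holm procedure.** Simulation of three outcomes, with common correlation 0, 0.3 and 0.6:
- Only one outcome has an effect of that size: about 65-66% for that outcome.
- All three have it: about 75%, 74% and 73% per outcome respectively.

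**4. Each primary outcome at 37 v 23 (noncentral t, quoted level SDs).** The detectable difference at 80% power is 0.757 SD at 0.05 and 0.881 SD at 0.0167.

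| Outcome | Power for a 10% difference, 0.05 | Same, 0.0167 | Detectable, 0.05 | Detectable, 0.0167 |
|---|---|---|---|---|
| Isoprostanes | 82% | 67% | 5.30 (9.8% of mean) | 6.17 (11.4%) |
| PWV | 42% | 26% | 1.82 (15.9%) | 2.11 (18.5%) |
| Pentraxin-3 | 15% | 7% | 0.227 (30%) | 0.264 (35%) |

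Isoprostanes show that the two defects are separate. On the quoted figures this outcome does reach 80% at 0.05, yet it falls to 67% at the first Holm step.

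**The case against.** Four points can be made against this.

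- **The 65% is conditional.** A reader might infer that the trial has about 65% power. The document does not support that. The figure comes from choosing d = 0.757 so that power at 0.05 is 80%, whereas the protocol's own pentraxin-3 effect is d = 0.25. This stands.
- **The first step is the worst case.** The protocol hypothesises an advantage for peritoneal dialysis on all the primary measures. If all three effects were of that size, the loss per outcome is about 5-7 points rather than 15, and the chance of at least one rejection is about 85-96%. This also stands, but none of the simulated cases restores 80% for an individual outcome.
- **The Holm family is inferred.** A reader might take it as stated that the three primary P-values form the family. The Statistical analysis section does not say so, and it also covers baseline comparisons and unadjusted and adjusted models. Three is the natural reading, since two groups and one slope per patient give one unadjusted contrast per primary outcome. A larger family would make the first threshold stricter than 0.0167.
- **The SDs do not describe the analysed quantity.** They are SDs of levels, while the test compares rates of change. The per-outcome figures therefore illustrate the quoted inputs and are not the power of the planned test.

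It can also be said that the non-reproducible 23 is the larger fault. That is true, but correcting it at an unadjusted 0.05 would leave this mismatch in place.

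**Conclusion.** The mismatch is real: the sizing uses 0.05 for one outcome, and the analysis corrects for several. Assuming two-sided tests and a three-outcome family, a comparison with true 80% power at 0.05 has about 65% at the first Holm step. Under the full procedure it has about 73-75% if all three effects are that size and about 65% if only one is.

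The point does not extend to a claim about the trial's actual power. That would need the SD of the rate of change, which the article does not give. On the quoted pentraxin-3 inputs the 80% starting point does not exist: power is about 15% at 0.05 and 7% at 0.0167. The Holm shortfall comes on top of that defect and is the smaller of the two. It should be corrected at the same time.

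**What to change.** Make the change when Sample Size Estimates is corrected for the 23:

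- Keep the Holm correction and the 80 enrolled, and state in Statistical analysis that the Holm family is the three primary outcomes.
- Do not claim 80% power.
- For each primary outcome at 37 v 23, state power and detectable difference at 0.0167 beside 0.05.
- Use an SD of the rate of change where one is available. Otherwise label the quoted level SDs as an assumption.

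The cost is one short table and a less favourable stated figure. No extra patients are needed, and the Holm procedure stays as it is.

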## Discussion

The objective of this study is to assess whether peritoneal dialysis will have less effect on arterial stiffness, vascular function, myocardial structure and function, oxidative stress and inflammation than hemodialysis. Comparing the effects of renal replacement therapy modalities on surrogate cardiovascular markers over time will provide unique important information to assist in the treatment of patients with ESKD. Data from this trial may also lead to a larger scale study assessing the effect of dialysis modality on major cardiovascular endpoints.
